### Blinding to the Nature of the Intervention

The research staff involved in clinical assessments are kept blinded to the nature of the allocated treatment. Due to the nature of the intervention, blinding of participating parent-child dyads has not been possible. To maintain the blinding of outcome assessors, parents are repeatedly instructed not to talk about the intervention they received with the assessors. The success of the blinding of the outcome assessors is tested by asking them the following question: “To which group is this child assigned according to your opinion?” Possible answers are as follows: “Control group: I know for sure,” “Intervention group: I know for sure,” “Control group: I think so,” “Intervention group: I think so,” and “I do not know” [36,37].

### Intervention Development

The MRC guidance on developing and evaluating complex clinical health care interventions was utilized in development and evaluation of the TOHI [30]. Prior to this study, the feasibility of the TOHI was investigated in a small-scale feasibility study and evaluated through semistructured interviews with stakeholders, including oral health professionals, OHCs, youth health care professionals, and parents. The resulting findings were instrumental in the study design and were used to refine the TOHI and adapt it to participating WBCs in the trial. Textbox 1 presents the conceptual framework for the TOHI. A full description of the TOHI, following TIDieR reporting guidelines [32], is available in Multimedia Appendix 1. The different components of the TOHI are described below.

Conceptual framework of the Toddler Oral Health Intervention.Components of the Toddler Oral Health InterventionUsing well-baby clinics to reach parents with newborn childrenUsing the Non-Operative Caries Treatment And Prevention Method for individual risk assessment and preventive oral careUsing motivational interviewing as the main tool to elicit internal motivation for desired behaviorUsing the Health Action Process Approach behavioral theory to guide the intervention based on underlying determinants of behaviorExpected mediators and secondary outcomesIncreased self-efficacyIncreased outcome expectanciesIncreased risk perceptionIntention forming for favorable oral health behavior; oral health coaches will explore barriers to and facilitators of favorable oral health behavior and focus on action planning and coping planning for favorable oral health behaviorAction and maintenance of favorable behavior; if necessary, oral health coaches will work on recovery self-efficacyOral health behaviorsTwice-daily toothbrushing with fluoride toothpasteImproved dietary habits with respect to oral health (eg, limiting sugar intake and the use of bottle-feeding, and drinking water more often)Primary oral health outcomeReduced cumulative caries incidence

### Interventions

In both the intervention and the control group, all dyads received or are receiving preventive child health care at the WBCs, which are regulated under the Public Health Act 2008. When a baby is registered in a municipality in the Netherlands, parents receive an invitation from the nearest WBC for a series of at least 13 appointments between birth and the age of 4 years. The goals of this preventive health care program are to monitor growth and development, detect health and social problems (or risk factors) at an early stage, screen for metabolic conditions and hearing in the newborn, deliver the national vaccination program, and provide advice and information on health [14]. According to the Public Health Act, this advice includes brief oral health promotion, such as the use of fluoridated toothpaste (at 500 ppm-750 ppm) and the advice to visit an oral health professional within the first year of life (Dutch Public Health Act, Article 6, paragraph 1, Dutch Public Health Decree). Dyads enrolled in the intervention group receive the TOHI in addition to this preventive health care program. Dyads enrolled in the control group receive only the usual care that all children receive at all WBCs in the Netherlands.

The TOHI builds on four components: (1) visiting an OHC at a WBC, (2) training OHCs to work accord to the NOCTP method, (3) using MI, and (4) using HAPA. The general understanding underlying the TOHI is that caries is a localized process and to a large extent can be prevented by brushing the teeth with fluoride toothpaste and lowering the frequency of sugar intake. With this understanding in mind, the OHC aims to create awareness among parents that through establishing adequate oral health behavior, they can effectively contribute to preventing caries in their children. The standardized protocol of the NOCTP method contributes to a uniform and transparent approach for OHCs and parents [19]. The method assigns 1 point based on parental cooperation and motivation, measured by the child’s oral hygiene and whether they follow the key oral health messages of the Ivory Cross national guidelines [38], and 1 point for active or incipient caries or lesions (Table 1). MI is used in the TOHI to elicit parents’ internal motivation and explore barriers and facilitators for desired oral health behavior. Finally, HAPA is a hybrid behavioral model that explicitly outlines 2 different phases of health behavior change: a motivational, intention-forming phase and a volitional phase in which translation of intention into action takes place [25]. Guided by HAPA, the OHCs focus on motivational and self-regulatory processes, such as self-efficacy, planning, and action control, which have been shown to be mediators in translating intentions into behaviors [29]. The OHC combines the NOCTP protocol with an intervention guided by HAPA and MI skills to determine which aspects of behavior need to be addressed for a tailored intervention.

**Table 1 table1:** Criteria for caries risk assessment, recall interval, and intervention.

Caries risk score	Risk	Intervention	Interval
0	Low	Periodic oral examination	Combined with scheduled well-baby clinic appointment within 6 to 12 months
1 (without active caries lesions)	Average	Shortened interval for periodic oral examination and exploration of barriers to and facilitators of self-care agreements	Combined with scheduled well-baby clinic appointment within 3 to 6 months or extra appointment when indicated
1 or 2 (with active caries lesions)	High	Shortened interval for periodic oral examination and exploration of barriers to and facilitators of self-care agreements; if necessary, referral to a dental office for fluoridation or treatment of caries lesions or incipient caries lesions	Combined with scheduled well-baby clinic appointment within 1 to 3 months or extra appointment when indicated

### Procedures of the TOHI

Face-to-face, 10-to-20-minute appointments with an OHC were combined with the child health care appointments at the WBC at the ages of 6 or 8, 11, 15, 18, 24, 36, and 42 months. Every appointment with the OHC started with an assessment of the child’s caries risk, following the NOCTP protocol. Subsequently, the OHC adjusted the oral health promotion to this risk by targeting the mediating determinants according to the HAPA, depending on the parents’ health behavior phase. When the intention was formed, self-care agreements were made in the volitional phase that focused on planning and action control to translate intentions into behaviors. Additionally, ambivalent feelings and barriers or facilitators to self-care agreements were explored using MI to stimulate intrinsic motivation and reinforce parents in existing positive behavior. According to the NOCTP protocol, when an increased caries risk was detected, the OHC could decide to schedule an additional appointment. If incipient caries lesions were detected, parents were educated on how to clean the caries lesion, and the use of fluoride toothpaste was again emphasized. When dental treatment for caries was deemed necessary, the OHC referred the participants to a dental clinic.

### Materials Used for the TOHI

A penlight and disposable materials (eg, cotton rolls to dry elements, dental mirrors, and wooden toothpicks to detect dental plaque on elements) were used for oral assessments by the OHC. In addition, the OHC used predefined paper patient records to ensure efficient and uniform reporting. These paper records contained age-related oral health topics to discuss, a caries risk assessment according to the NOCTP protocol, and an assessment of the parents’ oral health behavioral stage. The final caries risk and behavioral stage guided the OHC to follow-up actions, such as which mediating determinants from the HAPA should be addressed with the intervention (Multimedia Appendix 2). Parents in the intervention group received a specially developed TOHI booklet at baseline. This booklet was developed for 2 reasons. First, it contained oral health reports for each appointment with the OHC, which effectively communicated the child’s caries risk to the parents. These reports also covered agreed self-care actions to reduce caries risk. Together with the parents, the OHC examined and recorded the barriers to self-care actions and the mediating determinants of self-efficacy, action planning, and coping planning in these reports (Multimedia Appendix 3). Finally, the booklet covered essential oral health information and provided tips and tricks that the OHC could refer to.

### Oral Health Coaches and Training

Eligible OHCs for this study had a background in dentistry (they were dentists, dental hygienists, or dental assistants). They were prevention-minded, trained (or willing to be trained) in the NOCTP method, had good social communication skills, and had experience in pediatric dentistry. In addition, all OHCs received training in the TOHI delivered by a certified MI trainer and the principal investigator, who are both experienced in training oral health professionals and students in NOCTP, HAPA, and MI. A pediatric dietitian provided extra training on infant and toddler nutrition related to oral health. The first training session took place before the study started. Subsequently, training continued every 3 to 4 months for the duration of the study. During this training, the focus was on recognizing stages of health behavior, using HAPA, and developing advanced MI skills, such as recognizing and managing behavioral resistance and detecting ambivalence. Learning these skills takes time and is an ongoing process. Therefore, the training consisted of presenting practical examples of (successfully resolved) complex cases provided by the OHCs, role-playing, and peer feedback. In addition, the MI trainer provided individual feedback via self-recorded audio fragments that were uploaded by the OHCs. These audio fragments were assessed biannually with the Motivational Interviewing Treatment Integrity (MITI) [39] system by an independent MI expert. The results of the intervention fidelity will be analyzed and prepared for an original process evaluation article alongside the article reporting the results of the effectiveness study.

### Design of Data Collection

The outcome measures and additional data were collected with online questionnaires at baseline and with online questionnaires and clinical examinations when the children reached the ages of 24 and 48 months. Table 2 provides an overview of measurements and timepoints.

**Table 2 table2:** Measurements and timepoints.

Timepoint		Study period			
		–T1^a^	T0^b^	T1^c^	T2^d^
**Enrollment**					
	Eligibility screening	✓^e^			
	Informed consent	✓			
	Allocation	✓			
**Interventions**					
	Toddler Oral Health Intervention performed at ages 6-8, 11, 14-15, 18, 24, 30, and 36 months		✓	✓	✓
	Care as usual		✓	✓	✓
**Primary outcome**					
	Clinical assessment of cumulative caries incidence with Merged International Caries Detection and Assessment System [40]				✓
**Secondary outcomes**					
	Clinical assessment of average number of decayed, missing, and filled surfaces and teeth with Merged International Caries Detection and Assessment System			✓	✓
	Clinical assessment of person time at risk for first cavity with Merged International Caries Detection and Assessment System and incidence density			✓	✓
	Clinical assessment of consequences of untreated dental caries with the PUFA (visible pulpal involvement, ulceration caused by dislocated tooth fragments, fistula, and abscess) index			✓	✓
	Clinical assessment of presence of dental plaque with Simplified Oral Hygiene Index, 6-surface method [41]			✓	✓
	Online questionnaire assessment of oral health behavior with self-developed items		✓	✓	✓
	Online questionnaire assessment of psychosocial constructs of the Health Action Process Approach items (action self-efficacy, risk perception, outcome expectancies, intention, action planning, coping planning, and action control), adapted from Gholami and Schwarzer (2014) [42]		✓	✓	✓
	Online questionnaire assessment of oral health–related quality of life with the Early Childhood Oral Health Related Quality of Life [43] scale			✓	✓
	Online questionnaire assessment of child cooperativeness at oral examinations with the Frankl behavior scale [44]			✓	✓
**Compliance, fidelity, and cost outcome measures**					
	Total care delivered by oral health coach, assessed by frequency and time in minutes as reported by the oral health coach			✓	✓
	Reasons for and number of visits to a dental clinic (other than Toddler Oral Health Intervention), assessed by parent interviews				✓
	Oral health coach mastery of motivational interviewing competencies, assessed by applying Motivational Interviewing Treatment Integrity codes to audio recordings [39]		✓	✓	✓

^a^–T1: screening and allocation.

^b^T0: baseline.

^c^T1: follow-up at age 24 months.

^d^T2: follow-up at age 48 months.

^e^✓: measurement or action performed at this time point.

### Training of Outcome Assessors

The clinical outcome measures were collected by trained and calibrated dentists or dental hygienists in an assessor-blinded manner. The assessors were experienced in the use of the International Caries Detection and Assessment System (ICDAS) codes [40] for teaching or research purposes. Therefore, the training consisted of the online International Caries Classification and Management System (ICCMS) core e-learning [45] system and an online interrater reliability test developed for this study. This test presented 20 expertly verified high-quality pictures with different merged ICDAS scores in random order. If necessary for calibration, additional norming meetings were organized to maintain the performance of the assessors for the duration of the study.

### Outcome Assessments

At 24 and 48 months, a knee-to-knee examination (Figure 2) is completed with the assistance of the parents or caregivers. The selected tooth surfaces are scanned from the incisal to the gingival edge with a toothpick to determine the presence of dental plaque. Next, the child’s teeth are cleaned and dried with cotton rolls or gauze to enable an adequate view of the tooth surfaces and systematic examination of each tooth for the presence of caries or incipient caries. Findings are recorded in an online case record form developed for this study by an assistant. If no assistant is available, an audio recording is used so that the assessor can work efficiently and speak their findings aloud, preventing recall bias in later reporting. In cases with findings such as dentine caries, caries-related inflammation, and eruption failure of the primary teeth, parents receive a letter with the advice to visit a dentist and the reasons for doing so. If necessary, the OHC provides a list of nearby dentists. After dental treatment, children in the intervention group return for follow up with the OHC.

**Figure 2 figure2:**
[figure not shown]
Knee-to-knee position for oral examination.

### Primary Outcome

The cumulative caries incidence at the age of 48 months will be assessed by merged ICDAS [40] scores. These merged scores differentiate teeth as being sound or having initial, moderate, or severe caries.

### Secondary Outcomes

The average dmfs/dmft number and the caries incidence density (person-time at risk to the first cavity) will be calculated from the merged ICDAS scores. Consequences of untreated dental caries will be measured using the PUFA (visible pulpal involvement, ulceration caused by dislocated tooth fragments, fistula, and abscess) Index [46]. The presence of dental plaque will be determined with the 6-surface method of the Simplified Oral Hygiene Index [41]. Child cooperativeness during the outcome assessments will be documented by clinical assessors using the modified Frankl behavior scale [44].

Behavioral change over time will be assessed based on self-reported oral health behavior and psychosocial constructs from the HAPA, measured with online questionnaires at baseline, age 24 months, and age 48 months. The early childhood oral health–related quality of life will be measured using the Early Childhood Oral Health Impact Scale [43].

### Demographics and Patient Characteristics

The demographic characteristics include the children’s age, sex, family composition, mother’s highest educational attainment according to the International Standard Classification of Education [47], and health literacy measured with the 16-item European Health Literacy Survey Questionnaire (HLS-EU-Q16) [48].

### Design of Data Analyses

All analyses of the effectiveness of the TOHI will make use of the intention-to-treat principle. To prevent biased principal data analysis, concealment will be maintained during data analysis. The blinding of the study comparison will be broken only after the completion of data analysis for the evaluation of outcomes for children at the age of 48 months. After data cleaning and prior to data analysis, the amount and patterns of missing data will be explored. Sensitivity analysis will be used to explore the impact of missing data. The 3 following scenarios will be assumed: stability over time (last value carried forward or backwards to replace missing value), best case (largest positive change score observed to replace missing value), and worst case (largest negative change score observed to replace missing value).

The intervention effects for the cumulative caries incidence at 48 months and the average dmfs/dmft will be compared as the risk difference (additive scale), numbers needed to treat, and the relative risk (multiplicative scale), all with the 95% CI. Effects for subgroups (ie, WBC, education level of the mother, and health literacy) will be evaluated with interaction terms in a multivariate regression analysis. To determine incidence density and person-time at risk, the median and mean between-group differences in caries incidence (or the person-time to first caries lesion) will be based on a Kaplan-Meier analysis and incidence differences and ratios. In addition, when applicable, Cox proportional hazard regression analysis will be applied to explore relations with independent variables. Between-group differences at the age of 24 months will be assessed for the secondary outcomes, notably changes in the behavioral determinants (defined according to the HAPA), plaque, and self-reported oral health behavior, using linear regression analysis. Results from all analyses will be presented with the 95% CI. For all analyses, the SEP stratum will be used as the primary covariable, while sociodemographic characteristics for which a baseline difference is observed will be used as secondary covariables. Such postrandomization differences between groups will be explored using descriptive statistics. A difference of 20% for discrete variables, a full standard deviation (pooled) for normally distributed data, and a quartile for nonnormally distributed data will be used as thresholds for similarity.

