This paper describes a detailed research protocol to assess the effectiveness of the TOHI as an addition to usual WBC care, compared to usual WBC care only, in children aged up to 48 months. We hypothesize that the TOHI as an addition to usual care will reduce cumulative caries incidence at the age of 48 months (ie, the primary outcome measure), the sum of the number of decayed, missing, and filled surfaces and teeth (dmfs/dmft), the caries incidence density (person-time at risk to the first cavity), the presence of dental plaque, and the consequences of untreated caries (ie, secondary oral health outcome measures). We will study and report on (1) the oral health outcomes, (2) the behavioral outcomes, and (3) the balance between costs and effects of the TOHI.

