### Sample Size Calculation

Previous studies show that the average number of caries lesions in Dutch children at the age of 5 years is 4.5 (SD 4.5) [12]. This information was used for study size estimation using G*power 3 [34]. This showed that the intervention group needed at least 149 participants to demonstrate a reduction in cumulative caries incidence of at least 30% with a statistically significant Mann-Whitney *U* test allowing for statistical power (1-β) of .8 and a 2-sided α of .05 as a threshold for statistical significance. With an anticipated 30% loss to follow up, the aim was to include at least 200 participants per group.

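### At 48 months the only effect measures stated for average dmfs/dmft are risk difference, NNT and relative risk, which need a proportion and do not fit a count

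*Protocol article*

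**What the plan says.** The analysis section of the protocol article (Design of Data Analyses) treats two outcomes in one sentence. For cumulative caries incidence at 48 months and for dmfs/dmft alike, it says that "the average dmfs/dmft will be compared as the risk difference (additive scale), numbers needed to treat, and the relative risk", each with a 95% confidence interval.

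Three other places say what kind of variable dmfs/dmft is:

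- The Introduction calls it "the sum of the number of decayed, missing, and filled surfaces and teeth (dmfs/dmft").
- The Secondary Outcomes section says: "The average dmfs/dmft number and the caries incidence density (person-time at risk to the first cavity) will be calculated from the merged ICDAS scores".
- Table 2 lists it among the secondary outcomes, ticked at 24 and 48 months, as "Clinical assessment of average number of decayed, missing, and filled surfaces and teeth with Merged International Caries Detection and Assessment System".

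None of these gives a threshold or converts the number into a yes/no outcome.

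The analysis section has one further sentence that could bear on dmfs/dmft: "Between-group differences at the age of 24 months will be assessed for the secondary outcomes, notably changes in the behavioral determinants", using linear regression. It is limited to 24 months. A Mann-Whitney test appears only in Sample Size Calculation.

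**The concern.** Risk difference, relative risk and NNT are functions of two probabilities. An average number of affected teeth or surfaces is not a probability, so the sentence names measures that do not match the variable. This is not a detail left open for an analysis plan. The article names specific measures for this outcome, and an analysis plan that followed the sentence would carry the mismatch forward.

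dmfs/dmft is the first-listed secondary outcome and describes how much caries a child has, not only whether there is any. If the sentence is followed literally, an NNT would be published for it. A reader would take that as the number of children to coach for one child to benefit. It would in fact be the reciprocal of the average number of teeth or surfaces spared per child.

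**Working it through.** **1. Type of variable.** The Introduction, Secondary Outcomes and Table 2 all describe a sum or an average number. No passage dichotomises it. The three named measures, with p1 and p2 as control and intervention risks, are:

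- risk difference = p1 − p2
- relative risk = p2/p1
- NNT = 1/(p1 − p2)

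Each p lies between 0 and 1, so the absolute risk difference is at most 1 and the NNT is at least 1.

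**2. Inputs for an illustration.** The article gives no planning figure for dmfs/dmft. The nearest is in Sample Size Calculation: "the average number of caries lesions in Dutch children at the age of 5 years is 4.5 (SD 4.5"), with a target "to demonstrate a reduction in cumulative caries incidence of at least 30" percent. Two assumptions are needed: that these lesion figures, from age 5 years, apply to dmfs/dmft at 48 months, and that the 30% applies to the count.

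**3. The plan's own sample size.** The section states 149 in the intervention group, with "statistical power (1-β) of .8 and a 2-sided α of .05". Using noncentral-t power with the asymptotic relative efficiency (ARE) factor for the Mann-Whitney test:

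- SD 4.5 in both arms (d = 1.35/4.5 = 0.30): 184 per group with a normal parent distribution, 203 with the minimum-ARE option.
- SD falling with the mean to 4.5 × 0.7 = 3.15 (pooled SD = √[(4.5² + 3.15²)/2] = 3.88, d = 1.35/3.88 = 0.348): 152 with minimum ARE.

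So 149 is approximately reproduced under an SD assumption that the text does not state. The present point does not depend on this. The 149 serves below only as a group size.

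**4. The named measures applied to the means.**

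- Intervention mean = 4.5 × (1 − 0.30) = 3.15.
- Difference = 4.5 − 3.15 = 1.35, which exceeds 1 and so cannot be a risk difference.
- 1/1.35 = 0.74, which is below 1 and so cannot be an NNT.
- Ratio = 3.15/4.5 = 0.70. The number is sound, but it is a ratio of means, not a relative risk.
- The usual variance term for a proportion, p(1 − p), would be 4.5 × (1 − 4.5) = −15.75, so a standard interval for a risk difference could not be computed.

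The impossible value depends on the assumed means. If the mean difference were below 1, its reciprocal would exceed 1 and look plausible, but it would still be children per tooth or surface and not an NNT.

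**5. Valid measures with the same figures, 149 per group.**

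| SD (control, intervention) | Difference in means (95% CI) | Ratio of means (95% CI) |
|---|---|---|
| 4.5, 4.5 | 1.35 (0.33 to 2.37) | 0.70 (0.53 to 0.93) |
| 4.5, 3.15 | 1.35 (0.47 to 2.23) | 0.70 (0.56 to 0.88) |

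The difference uses 1.35 ± 1.96 × √(SD1²/149 + SD2²/149). The ratio uses 0.70 × exp(±1.96 × √[(SD1/4.5)²/149 + (SD2/3.15)²/149]).

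**6. The same measures on a binary outcome.** Take an assumed control risk of one-third, the share that the Introduction gives for dentin caries at age 5. A 30% relative reduction gives a risk difference of 0.333 × 0.30 = 0.10 and an NNT of 1/0.10 = 10. There the three measures work as intended.

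**The case against.** The strongest reply is that this is compressed wording in a journal article. The sentence tags its measures as additive and multiplicative. For a count those scales correspond to a difference and a ratio of means, both valid. A full protocol or analysis plan may spell this out. This has force: two of the three measures can be rescued by relabelling. The NNT cannot, because it has no counterpart for a mean unless a cut-off is given.

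A reader might go further and infer that dmfs/dmft has no valid analysis anywhere in the plan. The article does not support that. The 24-month linear regression is stated for the secondary outcomes, its named examples are not exhaustive, and Table 2 has dmfs/dmft as a secondary outcome at 24 months. That sentence may therefore cover it at that visit. The gap is at 48 months.

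Three other inferences are tempting and also unsupported:

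- **A fixed exaggeration of benefit.** Taking 4.5 as the mean among an affected third gives overall means of 1.5 and 1.05 and a reciprocal of 1/0.45 = 2.2, against an NNT of 10, or about 4.5 times. But the sample size section gives 4.5 as the average in Dutch children, not in affected children, and the factor simply returns the assumed 4.5 lesions per affected child.
- **That dmfs/dmft was the sample size basis.** The section speaks of caries lesions and of cumulative caries incidence. It mentions neither dmfs nor dmft.
- **That splitting dmft at zero would merely repeat the primary outcome.** The primary outcome is scored in merged ICDAS grades that include initial caries. Nothing says that the dmf threshold is the same, and the text does not propose such a split.

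**Conclusion.** The point holds for 48 months. The only effect measures stated there for average dmfs/dmft are risk measures, and the outcome is a count with no cut-off. The NNT is undefined and the other two measures carry the wrong names. The mismatch follows from the definitions alone and needs no numerical assumption. The value of 0.74 is an illustration that rests on applying the age-5 lesion figures and the 30% reduction to dmfs/dmft at 48 months.

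The consequence is limited. This is one secondary outcome, and the same measures are appropriate for cumulative caries incidence if that is the proportion of children with caries. No multiple by which benefit would be overstated can be given from the article. The text should be corrected before the 48-month analysis, because it states a measure that cannot be interpreted.

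**What to change.** Restrict risk difference, NNT and relative risk to cumulative caries incidence. For dmfs and dmft at 48 months, each reported separately, state one or both of:

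- the difference in means with a bootstrap 95% confidence interval;
- the ratio of means with a 95% confidence interval from a count model suited to skewed data with many zeros, for example negative binomial regression with robust standard errors.

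Other count methods would also serve; what matters is that one is named in advance. Adjust for the SEP stratum, which the article already plans for all analyses, and for well-baby clinic, the other randomisation stratum. If an NNT related to dmfs or dmft is wanted, define the cut-off first. It would also help to say whether the 24-month linear regression is meant to include dmfs/dmft.

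The cost is one sentence in the analysis plan. No new data are needed, and the sample size and primary analysis do not change.

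### Time to first caries is to be summarised by Kaplan-Meier medians and means, although caries is examined only at 24 and 48 months and onset is therefore interval-censored

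*Protocol article*

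**What the plan says.** **Examinations.** Under Design of Data Collection, outcomes are collected with "online questionnaires at baseline and with online questionnaires and clinical examinations when the children reached the ages of 24 and 48 months". Outcome Assessments confirms this: "At 24 and 48 months, a knee-to-knee examination" is done. There is no clinical examination at baseline, and Table 2 ticks the first-cavity person-time outcome at the 24- and 48-month visits only.

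**Outcome.** Secondary Outcomes states that "the caries incidence density (person-time at risk to the first cavity) will be calculated from the merged ICDAS scores". The Introduction classes this outcome as secondary, but the Objective in the Abstract names incidence density in the trial hypothesis beside the primary outcome.

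**Analysis.** Design of Data Analyses commits to median and mean differences between the groups in caries incidence, or in its alternative form: "the person-time to first caries lesion) will be based on a Kaplan-Meier analysis", with incidence differences and ratios. It adds that, "when applicable, Cox proportional hazard regression analysis will be applied to explore relations with independent variables".

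**Event.** The Introduction, Table 2 and Secondary Outcomes speak of the first cavity; Design of Data Analyses speaks of the first caries lesion. Under Primary Outcome, the merged ICDAS scores include initial caries, so the two terms can mean different events.

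**The concern.** Kaplan-Meier curves and event-per-person-time rates need a date for each event. Two examinations do not supply one; they only sort children into three classes. A child who misses the 24-month examination and has caries at 48 months could have had it at any time before 48 months.

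The article names a right-censored method and two summaries, median and mean time, that depend directly on onset dates. It gives no rule for dating onset and names no interval-censored or grouped-time method.

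At stake is a secondary outcome that appears in the trial hypothesis. The promised medians may not exist or may simply return an examination age, and the mean difference may depend more on the dating convention than on the intervention.

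**Working it through.** The article gives no median, rate or hazard ratio for this analysis, so there is no plan figure to reproduce. The check asks what the stated schedule can deliver.

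**Inputs from the article:** examinations at 24 and 48 months; entry at 6 to 12 months; about one-third with dentin caries at age 5 (Introduction); a 30% reduction (Sample Size Calculation).

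**Assumptions:** the onset models below, and the 30% reduction applied to cumulative incidence at 48 months.

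**1. Median.** Take a constant hazard from 9 months.
- Control hazard: λ = −ln(2/3)/(60 − 9) = 0.00795 per month.
- Control incidence: F(24) = 1 − exp(−15λ) = 11.2%; F(48) = 1 − exp(−39λ) = 26.7%.
- Intervention: F(48) = 0.70 × 26.7% = 18.7%, so λ = −ln(1 − 0.187)/39 = 0.00530 and F(24) = 7.6%.
- Event-free at 48 months: 0.73 and 0.81. Neither curve reaches 0.50. The model medians, 9 + ln 2/λ, are about 96 and 140 months.
- For both arms to reach 50% by 48 months, control incidence must be at least 0.50/0.70 = 71%.
- If 70% were affected at 60 months (assumed, for example if initial lesions count), incidence at 48 months is 60% and 42%. Dated at the examination, the control median would be reported as 48 months (true 38.4), and the intervention median would not be reached.

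**2. Mean and rate, same model, everyone examined.** True mean caries-free time over 39 months is F(48)/λ. With onset dated at the examination it is 39 − 24 × F(24). The rate is 1200 × F(48)/mean time.

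| | Control | Intervention | Comparison |
|---|---|---|---|
| True mean time (months) | 33.53 | 35.24 | difference 1.70 |
| Examination-dated mean time | 36.30 | 37.17 | difference 0.87 |
| True rate per 100 child-years | 9.54 | 6.36 | ratio 0.67 |
| Examination-dated rate | 8.81 | 6.03 | ratio 0.68 |

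The control rate is 1 − 8.81/9.54 = 8% too low, and the mean difference is about halved. Simulating the same setting gives 0.88 against 1.71 months.

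**3. Increasing hazard, with missed examinations.** Assume Weibull onset with shape 1.8 from 8 months, risk at 48 months of 1/3 and 0.70 × 1/3 = 0.233, and a fraction m missing the 24-month examination.
- F(24) = 1 − exp{ln(1 − F(48)) × (16/40)^1.8} = 7.50% and 4.98%.
- True mean time (integral of the survival curve over 40 months): 34.86 and 36.49; difference 1.63.
- Examination-dated mean time is 40 − 24 × (1 − m) × F(24). With m = 20% it is 38.56 and 39.04; difference 0.48 (simulation: 0.49 against 1.64).
- Control rate: 1200 × 0.3333/38.56 = 10.4 against 1200 × 0.3333/34.86 = 11.5, about 10% too low. Recorded mean age of control cases is 43.7 months against a true 32.6.
- Unequal attendance: the difference is 1.80 × (1 − m in control) − 1.19 × (1 − m in intervention). With 30% and 10% missing it is 0.18; with 0% and 20% it is 0.84 (simulation: 0.20 to 0.85).
- The rate ratio stays at 0.68 to 0.70 across these patterns, against a true 0.67.

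**4. Limit of the last result.** In the 70% scenario of step 1 the ratio moves more, to 14.67/22.68 = 0.65 against 16.83/28.33 = 0.59. The ratio is therefore robust at about the incidence that the article suggests, not at every incidence.

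**The case against.** The article states no dating rule. Person-time and Kaplan-Meier can also be run on interval midpoints, and a condensed article may leave that rule to the full plan. With midpoints, the first model gives a control rate of 9.52 against 9.54 and a mean difference of 1.66 against 1.70. In the second model, with 20% missing the 24-month examination in both arms, the figures are 11.7 against 11.5 and 1.76 against 1.63. This stands: the 8-10% shortfall belongs to examination dating and is not a stated feature of the plan.

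Three stronger readings are tempting, and the document does not support them.
- **The median can never be estimated.** The one-third figure is national dentin caries at age 5. The clinics serve predominantly low to middle socioeconomic areas, and initial lesions may count, so more than half could be affected.
- **The comparison between arms is invalid or driven by who attended at 24 months.** The incidence ratio, which the article also plans, hardly responds to attendance in the illustrations. The mean difference does.
- **Cox regression is an equal fault.** It is conditional and exploratory, and is not named as the effect estimate.

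The article also plans missing-data sensitivity scenarios, including values carried forward or backwards. These touch the missed 24-month examination, but by filling in a value rather than by treating onset as lying in a wider interval.

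What remains is that the article does commit to median and mean differences from Kaplan-Meier. No dating rule lets two examinations locate a median more closely than the interval between them.

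**Conclusion.** The point holds for the median and mean summaries of a secondary outcome that is named in the trial hypothesis. If fewer than half of an arm is affected by 48 months, which is likely for cavities, that arm has no median. If more are affected, the median is known only to lie within an interval between examinations, and Kaplan-Meier returns an examination age if onset is dated there.

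The mean difference is sensitive to the dating rule. Under examination dating it falls to about half of its true value or less, and it shifts further if attendance differs by arm. Rates fall by about 8-10%, while the rate ratio is little changed at the incidence the article suggests. These sizes rest on the assumed onset curves, a 30% reduction and, in the second illustration, 20% missing the 24-month examination.

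The primary outcome, cumulative incidence at 48 months, is unaffected. The change should be made, but the trial's main conclusion does not depend on it.

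**What to change.** Before allocation is unblinded, replace the Kaplan-Meier sentence under Design of Data Analyses with an interval-censored analysis of first caries:
- Use a complementary log-log (grouped-time proportional hazards) model on the two intervals, up to 24 months and 24 to 48 months. Alternatively, use a parametric interval-censored model on exact examination ages, which also handles missed 24-month examinations.
- Report the hazard ratio with 95% CI and the cumulative risk at 24 and 48 months in each arm.
- Drop the median difference. Report a mean only as a restricted mean from the interval-censored model.
- Date onset from the blinded outcome examinations only. Under Procedures of the TOHI, coaches assess caries risk at every appointment, but only in the intervention arm; using those dates would add onset information to one arm alone.
- Use the same event, first cavity or first caries lesion, in the Introduction, Table 2, Secondary Outcomes and Design of Data Analyses, and state the merged ICDAS level that defines it.

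The cost is a change of wording in the analysis plan. Standard software fits these models, and no new data are needed.
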